**3. ABSTRACT:**

The burden of malaria is not equally distributed in Kenya. Some villages experience a higher exposure to malaria compared to neighbouring villages and even within villages some households are disproportionally affected. In the Rachuonyo district in the Kenyan highlands, this heterogeneity in malaria exposure is striking with parasite prevalence rates at schools ranging from 0% to >70%. The persistence of malaria in small geographical areas despite high coverage with insecticide treated nets (ITNs) and indoor residual spraying (IRS) may be partially explained by outdoor biting and resting of malaria vectors.

These insights in the micro-epidemiology of malaria transmission in Rachuonyo district suggest that a revision of malaria control strategies may be needed to successfully control and eliminate malaria. In the current study, we propose to determine the value of rolling out four targeted malaria control efforts simultaneously in reducing malaria transmission. These targeted control efforts include local upscaling of currently used IRS and ITNs in hotspots of malaria transmission. In addition, larviciding will be employed to target malaria vectors, also those that are less susceptible to IRS and ITNs as a consequence of outdoor feeding and resting. Lastly, the human infectious reservoir will be reduced by treating parasite carriers and their household members in hotspots of malaria transmission.

The impact of these targeted interventions will be assessed in the context of currently ongoing malaria control activities in a 2-year cluster randomized trial. In the cluster randomized trial up to 8 interventions clusters will be randomized to receive hotspot targeted interventions and compared with an equal number of control clusters where the (untargeted) malaria control activities continue. The intervention will be evaluated based on changes in parasite prevalence measured in community surveys inside and outside hotspots of malaria transmission.

We expect that this approach will not only reduce the burden of malaria in these hotspots (direct effect), but will also reduce transmission in the area as a whole by an indirect community effect (indirect effect). Areas with higher parasite prevalence are likely to maintain transmission in the area by forming the main source of infection for mosquitoes; mosquitoes subsequently spread malaria over a larger geographical region. If a hotspot targeted approach proves promising in the current cluster randomized trial, it has the potential to maximize the impact of malaria control efforts in all areas with heterogeneous malaria transmission.

This protocol falls under the larger Malaria Transmission Consortium (MTC) umbrella of projects which aims to investigate the effectiveness of programmatic activities against malaria and to develop standardized methods of estimating malaria transmission in different epidemiological settings. As such, this protocol complements those studies already on-going evaluating IRS vs. ITN centred strategies (e.g. SSC 1517, 1802, 1399, 1589, 2007) and together they will provide critical information to the DOMC on the most effective malaria control strategies in highland areas of Western Kenya.

**4. LIST & DEFINITIONS OF ABBREVIATIONS, ACRONYMS**

| ACT | Artemisinin Combination Therapy |
| --- | --- |
| AL | Artemether-Lumefantrine |
| CDC | Centers for Disease Control and Prevention |
| DSS | Demographic Surveillance System |
| DOMC | Division of Malaria Control |
| EDTA | Ethylenediaminetetraacetic Acid |
| ELISA | Enzyme Linked Immunosorbant Assay |
| FSAT | Focal Screening And Treatment |
| GFATM | Global Fund against AIDS Tuberculosis and Malaria |
| HRP-2 | Histidine Rich Protein-2 |
| IPTp | Intermittent Preventive Treatment in Pregnancy |
| IRS | Indoor Residual Spraying |
| ITN | Insecticide Treated Nets |
| KEMRI | Kenya Medical Research Institute |
| LDH | Lactate Dehydrogenase |
| LLIN | Long- Lasting Insecticide Treated Nets |
| LMP | Last Menstrual Period |
| LSHTM | London School of Hygiene and Tropical Medicine |
| RUNMC | Radboud University Nijmegen Medical Centre, the Netherlands |
| MOH | Ministry Of Health |
| MTC | Malaria Transmission Consortium |
| PCR | Polymerase Chain Reaction |
| PCPB | Pest Control Product Board |
| PDA | Personalised Digital Assistant |
| PMI | Presidents Malaria Initiative |
| PSI | Population Services International |
| RDT | Rapid Diagnostic Test |
| RUNMC | Radboud University Medical Centre |
| RR | Relative Risk |
| SCR | Sero Conversion Rate |
| SP | Sulphadoxine Pyrimethamine |
| WHO | World Health Organisation |

**5. Introduction/BACKGROUND:**

The risk of malaria is not uniformly distributed between districts, between villages and even between households from the same village. Some households are disproportionally exposed to malaria and malaria incidence in these households may be more than 5-fold higher than the village average [[1-3](#_ENREF_1)]. This heterogeneity in the burden of malaria at micro-epidemiological level is largely explained by variation in exposure to infected mosquito bites [[3](#_ENREF_3)] and complicates malaria control by resulting in large variations in the impact of interventions [[4](#_ENREF_4)]. While average levels of malaria transmission may decline in an area, strongholds of intense malaria transmission may persist. This has been observed during intensive malaria control efforts on Bioko island [[4](#_ENREF_4)] and persisting malaria hotspots on Zanzibar [[5](#_ENREF_5)] and Mali [[6](#_ENREF_6)] despite overall trends of reducing transmission intensity.

In the highlands of Western Kenya, malaria transmission is also highly variable despite universal high coverage rates with insecticide treated nets (ITNs) and indoor residual spraying (IRS). In Rachuonyo district, community surveys that were conducted in 2010 indicated parasite prevalences averaging 14.8% but ranging from 0% to 51.5%. School surveys that were conducted in the same year at 46 schools in the district revealed an even more marked variation in children aged 8-14 years where parasite prevalence was on average 25.8% but ranged from 0 to 71.4%. These findings indicate that the current control efforts are insufficient to control or eliminate malaria in parts of the district. One of the reasons that may underlie this apparent failure to interrupt local malaria transmission may be the presence of outdoor biting and resting mosquitoes. Work conducted by the Malaria Transmission Consortium in Rachuonyo has recently indicated that a sizeable proportion of mosquitoes may feed outdoors in the Kenyan highlands [[name] *et al.*, in preparation]. Outdoor biting vectors may remain largely unaffected by control tools that target indoor biting and/or resting mosquitoes like IRS and ITNs. Additional malaria control efforts may therefore be needed in areas where transmission persists: control efforts that reduce malaria transmission regardless of the biting or resting behaviour of the mosquito vector. These targeted interventions are likely to have an impact on malaria transmission in the entire district since small areas with higher malaria transmission intensity form important contributors to overall malaria transmission. Households that are exposed to higher numbers of infected mosquito bites consequently have a higher parasite load in humans. This clustering results in an amplification of malaria transmission: households that are highly exposed to infected mosquitoes also form an important source of malaria infection for uninfected mosquitoes that can spread malaria in the rest of the community [[7-9](#_ENREF_7)]. Hotspots of malaria transmission can thereby increase the efficiency of malaria transmission by a factor 2 to 4 [7-8].

In a recent survey, we have collected information to identify micro-epidemiological patterns in malaria transmission in the Rachuonyo District in the Kenyan Highlands. In this survey, we collected filter paper blood samples from ~3,200 households in an area of 100km^2^. Hotspots of malaria transmission are identified by determining spatial patterns in the prevalence of *P. falciparum* parasites and serological markers of malaria exposure [2-3, 10]. Compared to parasite prevalence rates, serological markers of malaria exposure and haemoglobin levels have the advantage of providing information on malaria exposure that is less susceptible to seasonal variations in the force of infection [3, 11-12]. In an area in Tanzania, serological markers of malaria exposure were recently found to have a sensitivity of 93% and a specificity of 85% in identifying hotspots of malaria transmission [[3](#_ENREF_3)].

In the current study we propose to target hotspots of malaria transmission in Rachuonyo with two purposes: i) reducing the burden of malaria in areas where current control measures have proven inefficient in controlling malaria; ii) reducing the overall burden of malaria by interrupting transmission in these areas that form catalysts for overall malaria transmission. Coverage with currently available tools will be upscaled in hotspots of malaria transmission. In addition to a targeted upscaling of IRS coverage and ITN coverage, done by the study team in close communication with the DOMC, we will target water bodies within hotspots that are likely to persist for more than a week and that are found to have *Anopheles* larvae with larvicidal agents. As well as vector control measures, we will aim to reduce the human infectious reservoir in hotspots by Focal Screening and Treatment (FSAT) campaigns where symptomatic and asymptomatic individuals in hotspots of malaria transmission are screened for the presence of malaria parasites and treated with artemisinin combination therapy. This intervention follows the Kenyan National Malaria Strategy for 2009-2017 that mentions as part of strengthening the disease surveillance capacity a similar approach of targeted screening and treatment of asymptomatic malaria infections, “*… strengthening capacity to test every fever case, following up positive cases with home visits, screening household members of the index case and treating those found positive for malaria.”*[[13](#_ENREF_13)] and objectives to treat asymptomatic infections in school children as part of the malaria-free school initiative [[13](#_ENREF_13)].

The impact of the hotspot targeted approach will be evaluated by cross sectional community surveys in which we determine the prevalence and density of malaria infections and malaria-specific immune responses.

**6. Justification OF THE INTERVENTION:**

Seasonal indoor residual spraying with insecticides and campaigns to increase bednet coverage in the highlands of Western Kenya have reduced the burden of malaria in Rachuonyo district. However, the impact of the interventions is variable across the district and several areas continue to have high parasite prevalence rates among the general population and particularly among school children. These observations indicate that the current control efforts are insufficient to control or eliminate malaria in the area and additional efforts are needed.

For a maximum impact, these additional interventions should specifically aim to reduce malaria where it is most prevalent, target both indoor and outdoor biting and resting mosquitoes and also reduce the human infectious reservoir [[14](#_ENREF_14)]. When targeted to hotspots of malaria transmission, these interventions are expected to be highly efficacious in reducing malaria transmission locally and throughout the district.

**7. MAIN OBJECTIVE:**

To evaluate the impact of hotspot targeted interventions with LLINs, IRS, larviciding and FSAT on malaria indices in the community.

# 8. Specific objectives AND HYPOTHESES TO BE TESTED:

1. To evaluate the impact of hotspot targeted interventions with LLINs, IRS, larviciding and FSAT on malaria parasite prevalence inside hotspots of malaria transmission [Ho = hotspot targeted interventions will not reduce malaria parasite prevalence inside hotspots]
2. To evaluate the impact of hotspot targeted interventions with LLINs, IRS, larviciding and FSAT on malaria parasite prevalence in the area surrounding the hotspots of malaria transmission [Ho = hotspot targeted interventions will not reduce malaria parasite prevalence in the areas surrounding malaria hotspots]
3. To evaluate the impact of hotspot targeted interventions with LLINs, IRS, larviciding and FSAT on serological markers of malaria exposure inside hotspots of malaria transmission [Ho = hotspot targeted interventions will not reduce serological markers of malaria exposure inside hotspots]
4. To evaluate the impact of hotspot targeted interventions with LLINs, IRS, larviciding and FSAT on serological markers of malaria exposure in the area surrounding the hotspots of malaria transmission [Ho = hotspot targeted interventions will not reduce serological markers of malaria exposure in the areas surrounding malaria hotspots]

**9. DESIGN AND METHODOLOGY:**

## a. General study design

This study is a cluster-randomized trial where we compare the impact of hotspot targeted interventions on malaria transmission. Up to 16 clusters will be defined based on currently ongoing activities with half receiving the interventions. In each of the intervention clusters, all 4 hotspot-targeted interventions will be superimposed on ongoing control measures: hotspots will be targeted with a combination IRS, LLINs, larviciding and FSAT. The other clusters will serve as controls; these areas will not be targeted.

The interventions will be evaluated in the context of ongoing malaria control efforts. In the entire study area current ongoing malaria control interventions will continue without interruption.

## b. Study site and population.

Ethnicity in Rachuonyo is predominantly of the Luo ethnic group. Local residents depend upon farming and cattle and goat herding for subsistence. Compounds are distributed broadly across a rolling landscape intersected with small streams and rivers. The main malaria vectors in the area are *Anopheles gambiae*, *An. arabiensis*, and *An. funestus*. Malaria transmission is seasonal, with two seasonal peaks in malaria cases reflecting the bimodal rainfall pattern, with the heaviest rainfall typically occurring between April and June, with a smaller peak between October and November each year. Most malaria is caused by *Plasmodium falciparum*. Community surveys that were conducted in 2010 indicated parasite prevalences averaging 14.8% but ranging from 0% to 51.5%. School surveys that were conducted in the same year at indicated an average parasite prevalence of 25.8% (range 0 to 71.4%).

Detailed cross-sectional surveys have been conducted in an area of 100km^2^ (5x20km) in Rachuonyo district to determine small-scale variations in malaria transmission intensity. (see figure 1). This area was sub-divided into 400 500m^2^ areas referred to as cells.

[figure not shown]

*Figure 1. The Rectangle indicates the area (5*20km) in Rachuonyo district where the activities will take place. Each dot is an individual household. White dots indicate the parasite prevalence in school surveys in the area in the year 2010; colour intensity indicates variation in the altitude. The proposed study area lies at an altitude of 1400-1550 meters.*

All structures in this 5 x 20km area were geo-located by remote sensing and 3,200 compounds were randomly selected for detailed characterization of malaria exposure. After informed consent, household characteristics were recorded for all houses that belonged to the selected compound. Temperatures were taken from each permanent resident of the selected compounds and individuals were asked to provide a single finger-prick blood sample for detection of malaria parasites by PCR [15], malaria-specific antibody responses by ELISA [[12](#_ENREF_12)] and haemoglobin concentration by HemoCue photometer [Angelholm, Sweden]. Febrile individuals were screened in the field using rapid-diagnostic tests [Paracheck, Orchid Biomedical Systems, India] and treated with first line artemisinin-combination therapy.

## c. Definition of clusters for interventions

## The data collected during the intensive cross-sectional surveys (SSC 1802) will be used to detect hotspots of malaria transmission in the study area based on malaria parasite prevalence and antibody responses. Hotspots will be defined as areas that are smaller than 1km^2^ with a level of transmission intensity that exceeds that in the surrounding area (in all directions). This will be indicated by a statistically significant higher parasite prevalence in combination with a statistically significant higher SCR and/or age-adjusted density of antibodies malaria antigens.

Malaria parasite prevalence will be determined by PCR-based detection of parasites based on the *P. falciparum* mitochondrial cytochrome b gene [15].

Malaria specific antibody responses will be quantified as the age-dependent seroconversion rate (SCR) for antibodies against malaria: antigens apical membrane antigen-1 (AMA-1), merozoite surface protein-1 (MSP-1_19_) and glutamate-rich protein (GLURP) [[12](#_ENREF_12)]. Antibody responses will be measured by standard ELISA methodology [12, 16] and the SCR will be determined by fitting a simple model to the age-dependent prevalence of antibody responses, as described in detail in publicly available protocols [16]. In addition, age-adjusted antibody densities will be calculated [17]. The SCR will be estimated for geographical subsets of 50 observations.

Hotspots will be of variable size and no quantitative estimate of the elevated transmission intensity inside hotspots can be given a-priori since this depends on the transmission intensity of the surrounding area [2-3,16]. Clusters will include hotspots and a surrounding ‘evaluation zone’ of 500m from the edge of the hotspot (see figure 2); this forms the unit of randomization. The grid structure that divided the study area into 250x250m cells, created as part of the baseline cross-sectional study will be used as easy references for the areas defined as hotspots. The size of a hotspot or intervention area will not be defined by the maximum mosquito dispersal range. We are not aiming to identify independent niches of malaria transmission. Minimum distance between hotspots will be 1km. Mosquito dispersal outside hotspots of malaria transmission is essential for the community effect and forms the cornerstone of our evaluation.

[figure not shown]

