## *Figure 2. Example of possible layout of hotspots (black blocks) and the surrounding areas (grey blocks) where hotspot targeted interventions will be evaluated). The depicted grid cells are 250x250m.*

## d. Intervention

Up to sixteen clusters will be defined as in the example shown in figure 2. Each cluster consists of a hotspot of malaria transmission and the area surrounding the hotspot 500m in each direction. In the entire study area current malaria control interventions will continue without interruption. In the intervention clusters (i.e. half of the identified hotspots), interventions will be superimposed on ongoing control measures: these intervention hotspots will be targeted with IRS, LLINs, larviciding and FSAT. All the intervention measures will be discussed in more detail in section f. ‘Procedures- Intervention Phase’ however, a brief overview is provided below.

*Indoor Residual Spraying (IRS)*

IRS will be carried out twice per year in all households in the intervention hotspots in the period preceding the long rainy season (March 2012) and six months later (September 2012). Meetings will be held with DOMC to discuss the optimal insecticide for use in the context of ongoing IRS activities in the district.

*Long Lasting Insecticide Treated Bednets (LLIN)*

All compounds in intervention hotspots will be visited in March 2012 and each house will receive a Long Lasting Insecticide Treated Nets for each sleeping space. The DOMC will be consulted about which type of LLINs should be distributed and how best to approach this, but activities will be undertaken by study personnel A follow-up visit is planned one month and 6 months after LLIN distribution to provide additional nets where needed and to monitor accurate use.

*Larviciding*

All mosquito larval habitats in all hotspots and evaluation zones will be mapped using handheld GPS systems in January. All habitats found to persist for more than a week within intervention areas will be treated with a larvicide that has been approved by the Pest Control Product Board and by DOMC, *Bacillus thuringiensis var. israelensis* (Bti) and/or *Bacillus sphaericus* (Bs). Larviciding will begin in March 2012 and continue weekly throughout the rainy season (until July 2012).

*Focal screen and treatment (FSAT)*

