## e. Sampling strategy and sample size calculation

The hotspot-targeted intervention will be evaluated inside and outside hotspots of malaria transmission. The latter is the main outcome measure of interest and forms the basis of sample size calculations. All available malaria simulation models indicate that malaria transmission in the area surrounding intervention hotspots would be considerably decreased because malaria transmission is effectively reduced/interrupted in those compounds that seed transmission to a larger geographical area [7-8, 19]. Because there are no published studies on the impact of hotspot targeted interventions, we determined the predicted impact of targeted interventions in our study area by one of the leading individual-based simulation model [19] using human, entomological and parasitological characteristics collected at our sites in Kenya. A previous study on the community benefits of insecticide treated nets in Asembo Bay, western Kenya, indicated that an indirect beneficial effect on malaria transmission may be limited to 500m from the intervention area [20]. We used this finding to define our evaluation zone surrounding the hotspots.

| [figure not shown] |
| --- |

***Figure 3. The predicted impact of untargeted and targeted interventions predicted by an individual-based simulation model.*** *Plotted are smoothed lines, the actual model estimates allow for seasonality.*

We modelled three scenarios in situations with a pre-intervention parasite prevalence in the human population of 5-15%: i) indoor residual spraying (IRS) in an untargeted approach, reaching 20% of the total population (black top line); ii) effective coverage with long lasting insecticide treated nets (LLINs) in an untargeted approach, reaching 80% of the total population (middle dashed grey line); iii) targeted IRS and 95% effective coverage with LLINs in the hotspots (bottom light grey line). The impact of larviciding is currently insufficiently parameterized to be included in the model [19].

We assumed a conservative estimate of the efficacy in detecting hotspots (75%, compared to 93% in Tanzania [[3](#_ENREF_3)]). Our simulations showed that targeted interventions can interrupt transmission completely, both inside and outside hotspots of malaria transmission, reducing overall parasite prevalence from 15% to <0.1%, in a manner that appears sustainable in the following years (see figure 3).

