**10. DATA MANAGEMENT:**

a. Data storage

All data from the questionnaires during cross-sectional surveys will be collected on PDAs and downloaded each evening into Microsoft Access. Paper records will be used as a back-up to the PDAs for recording visited households and RDT and anaemia results. All consents, assents, PDAs and computers to which data are downloaded will be locked so that only the principal investigators and data management staff will have access to the data. Data will be cleaned on an on-going basis.

b. Data analysis

To assess the impact of the intervention, methods appropriate for cluster-randomized trials will be used [30]. The primary outcome will be PCR-confirmed parasitaemia. The prevalence by PCR in each cluster will be calculated and the unadjusted risk ratio (RR), or mean difference between clusters will be calculated. An overall estimate of programme impact will be obtained, and 95% confidence intervals will be adjusted for observed between-cluster variance. Formal hypothesis testing will be undertaken using stratified unpaired t-tests. Adjustment for covariates will be undertaken replacing the cluster means and proportions with covariate-adjusted residuals from regression analysis of individual-level data.

One of the key outcomes of the study is the community-wide effect of hotspot targeted interventions. To address the question of the distance over which this community-wide effect exists, we will relate parasite prevalence and antibody prevalence to the distance from the centre of the hotspot in intervention and control clusters.

Additionally, the analysis adjusts for baseline characteristics on malaria infection, haemoglobin concentration and socio-economic status. Statistical analysis will be carried out using STATA^®^ software, version 10.0. (Stata Corporation, Texas, USA).

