Intervention participants will receive intensive malaria control for their household: IRS, LLINs, larviciding and in FSAT. These interventions are expected to have a direct and an indirect beneficial effect on the level of malaria the household is exposed to: IRS will reduce indoor mosquito exposure, LLINs will protect individuals from (infected) mosquito bites, larviciding will reduce indoor and outdoor mosquito exposure; FSAT will clear parasite carriage and provide 3-4 weeks of efficacious prophylaxis against malaria infections. These interventions are provided free of charge.

The wider community, i.e. those living in the vicinity of hotspots will not receive any direct benefits from the interventions, but are likely to experience indirect effects. Reductions in neighbouring areas with high malaria prevalence may result in reduced malaria transmission in the wider region.

*Benefits to participants in control area*

Participants in the control areas will not benefit from the interventions in the short term but will benefit from free screening and treatment for symptomatic malaria. However, the information that will be learned as a result of this study can benefit them in the future through more effective and targeted malaria control interventions and the possible overall reduction in malaria transmission that may ensue. There are plans for district-wide government-led interventions such as IRS to take place. All these will continue as planned and none will be withheld from the communities. Depending on the outcomes of the first year of the intervention, in consultation with the DOMC, to roll-out the most efficacious intervention/s to all hotspots in the study area.

*Community benefits*

The community benefit of the project is that we expect malaria transmission in the entire area to be reduced as a result of our hotspot targeted interventions. Free LLINs and intensive vector controlled will be offered to individuals residing in some of the strongholds of malaria transmission in Rachuonyo district; plausibly leading to a direct benefit to this part of the population that is most affected by malaria. The MOH is also expected to benefit from this study by gaining a lot of information on the status of malaria transmission in this area of Rachuonyo district as the findings will be shared with them. The Government of Kenya may also benefit by improving malaria control strategies and targeting efforts where they can be most effective.

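### Intervention and control evaluation zones can share a border with no buffer, so the main contrast is diluted if the indirect effect reaches beyond 500 m, and the planned distance analysis cannot show whether it does.

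*Protocol*

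**What the plan says.** **Layout.** Protocol section 9c states: "Clusters will include hotspots and a surrounding ‘evaluation zone’ of 500m from the edge of the hotspot". Section 9d repeats it: "Each cluster consists of a hotspot of malaria transmission and the area surrounding the hotspot 500m in each direction". Hotspot plus zone is the unit of randomisation. On spacing, section 9c says only: "Minimum distance between hotspots will be 1km". It does not say whether this runs from edge to edge or centre to centre. No buffer is required, and no extra separation is set between hotspots in opposite arms. Section 9c also states: "We are not aiming to identify independent niches of malaria transmission".

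**Reach of the indirect effect.** Section 9e relies on an earlier bednet study in western Kenya that "indicated that an indirect beneficial effect on malaria transmission may be limited to 500m from the intervention area", and uses it to set the zone width. The abstract says that the approach "will also reduce transmission in the area as a whole by an indirect community effect". Section 5 expects an impact across the whole district. Under community benefits, section 12b says "we expect malaria transmission in the entire area to be reduced as a result of our hotspot targeted interventions". The same section also says that people in control areas gain nothing from the interventions in the short term.

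**Analysis.** Section 9e makes parasite prevalence in the evaluation zone the basis of the sample size. Section 10b adds a distance analysis, introduced with the words "To address the question of the distance over which this community-wide effect exists". Its distance variable is distance from the centre of the hotspot, in intervention and control clusters.

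**The concern.** Where two zones of opposite arms touch, a control compound at the shared border is 500 m from a treated hotspot. That is the same distance as the outermost compounds of the intervention zone, yet it counts as unexposed. Conversely, an intervention-zone compound there is 500 m from an untreated hotspot that may go on seeding infection. If the indirect effect does not stop at 500 m, both mechanisms pull the two arms together on the outcome for which the trial is sized.

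The distance analysis would not reveal this. Measured from a compound's own hotspot, distance in the intervention arm ends at the outer limit of the zone. Control compounds close to an intervention hotspot enter as if untouched. The question of how far the effect reaches therefore cannot be answered beyond the zone.

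**Working it through.** **1. Geometry.** Inputs are the minimum separation of 1,000 m and the zone width of 500 m (sections 9c, 9d).

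- Edge to edge: gap between zones = 1,000 − 2 × 500 = 0 m.
- Centre to centre, with hotspots of width w: gap = 1,000 − w − 2 × 500 = −w, so the zones would overlap.
- On the line between two hotspots 1,000 m apart edge to edge, the control zone lies 500 to 1,000 m from the edge of the intervention hotspot.

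**2. Are close neighbours plausible?** The study area is 5 × 20 km = 100 km² (section 9b), with up to 16 clusters (section 9a) and hotspots below 1 km² (section 9c). Assume 16 square clusters, each with side equal to hotspot side + 2 × 0.5 km.

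- Hotspot side 0.5 km: 16 × 1.5² = 36 km².
- Hotspot side 1 km, the upper limit: 16 × 2² = 64 km².

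Touching zones are plausible. These areas do not show that they will occur.

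**3. Dilution of the contrast.** The plan's own contrast is 10% versus 5%, a reduction of 1 − 5/10 = 50%. Let f be the share of the 5-point fall that also reaches control zones. Control prevalence is then 10 − 5f. The documents give no value for f, so a range is shown.

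| f (assumed) | Control | Intervention | Apparent reduction |
|---|---|---|---|
| 0 | 10% | 5% | 50% |
| 0.25 | 8.75% | 5% | 1 − 5/8.75 = 43% |
| 0.50 | 7.5% | 5% | 1 − 5/7.5 = 33% |

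**4. What this does to power.** The standard unmatched cluster formula is c = 1 + (1.96 + 0.84)² × V/(p0 − p1)², with V = p0(1 − p0)/n + p1(1 − p1)/n + k²(p0² + p1²). Section 9e gives n = 300 and k = 0.5. It prints the two z values only for the within-hotspot calculation; they are assumed to apply here too.

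- At f = 0: V = 0.000300 + 0.000158 + 0.003125 = 0.003583, and c = 12.25, that is 13 clusters per arm. The stated 8 is not reproduced. That is a separate matter, but it means there is no reserve to absorb dilution.
- Power with 8 per arm is Φ(√(7/V) × (p0 − p1) − 1.96). This gives about 60% at f = 0, 45% at f = 0.25 and 27% at f = 0.50.
- If k were 0.38, close to the value at which 8 clusters would suffice, the same three figures are 79%, 63% and 39%.

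**5. The statements on reach, side by side.** The 500 m figure in section 9e is hedged and comes from bednets alone, whereas this package adds spraying, larviciding and FSAT. The abstract, section 5 and the community-benefit text in section 12b expect an effect over the area or district in which the control clusters lie. The control-area text in section 12b points the other way in the short term. These cannot all guide the same analysis without reconciliation.

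**The case against.** The spacing agrees with the protocol's stated premise. If the effect ends at 500 m, a 1 km edge-to-edge minimum is exactly twice the zone width, and a control zone begins where the effect stops. Contamination would then be close to nil. Section 9e is also the only place that puts a distance on the reach; the wider statements come from the abstract, the background and the benefits section. The protocol openly declines to seek independent transmission niches. All of this stands, and it is why the point is conditional.

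Three stronger readings are tempting, and the documents do not support them.

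- *That the protocol predicts contamination of its controls.* Its wording is inconsistent, and section 12b denies a short-term benefit in control areas. The simulation in section 9e shows near-elimination inside and outside hotspots, but the text does not say that it leaves half the hotspots untreated, as the trial does.
- *That spillover would wipe out the main effect, or that a null result would be uninterpretable.* The scenarios above weaken the contrast without removing it. Only f near 1 would remove it, and nothing in the documents gives f. Control-zone prevalence can also be compared across matching seasons in 2012 and 2013 (section 9g), although secular trends limit that comparison.
- *That equal allocation makes close opposite-arm neighbours likely.* Allocation odds say nothing about distance.

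It may also be said that the choice of distance variable belongs in a statistical analysis plan. But section 10b already fixes one, and that choice is the one at issue.

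**Conclusion.** The point holds as a conditional weakness. Opposite-arm zones can share a border without a buffer, and the protocol's statements on the reach of the effect conflict. If the effect extends beyond 500 m, the evaluation-zone contrast is biased towards no effect. A 50% reduction would appear as 43% or 33% under assumed spillover shares of 25% or 50%. If the effect truly ends at 500 m and spacing is measured edge to edge, the bias is negligible. The distance analysis as written cannot tell these cases apart, because it looks only at the compound's own hotspot. The result rests on the edge-to-edge reading and on spillover shares that the documents do not give. How many opposite-arm zones will touch is also unknown.

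**What to change.** Keep the randomised comparison of evaluation zones as primary, and make these changes:

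- **Reconcile the statements on reach** in the abstract and in sections 5, 9e and 12b. State in section 9c how the 1 km is measured.
- **Redefine exposure in the section 10b distance analysis.** For every surveyed compound in both arms, use distance to the nearest intervention hotspot of any cluster, with distance to the nearest untreated hotspot as a covariate. Control-zone compounds then inform reach beyond 500 m. Coordinates are already recorded (Appendices C and E).
- **Add one supportive sensitivity analysis** of the evaluation-zone outcome. It omits, symmetrically in both arms, compounds close to a hotspot allocated to the opposite arm, with the distance fixed in advance.
- **State the limit on interpretation:** the main contrast is likely to underestimate the effect if the effect extends beyond 500 m.

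The cost is two derived variables and one extra analysis, with no new fieldwork. The sensitivity analysis loses sample. With a 1 km cut-off and square hotspots 0.5 to 1 km wide, one opposite-arm neighbour touching along a full side removes about 32% to 35% of a zone's area. It also cannot restore an unexposed control if the effect is area-wide, so it should be labelled supportive only.
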